**Methods and analysis:**

This is a single-centre, prospective, phase II randomised controlled trial. From January 2022, all eligible patients will be recruited. 100 patients will be randomised to the intervention arm, that is, nadroparin two times per day 5700 AxaIU, or the control arm, that is, nadroparin once daily 2850 AxaIU in patients with body weight ≤100 kg or once daily 5700 AxaIU in patients with body weight >100 kg, both for up to 21 days. The trial includes a 6-month follow-up period. The primary objective is 30-day mortality rate. Secondary outcomes include assessment of DCI, complications during admission, discharge location, clinical outcome (modified Rankin Scale), quality of life and total healthcare costs at 3 and 6 months follow-up.

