**Trial registration number:**

NCT04507178.

STRENGTHS AND LIMITATIONS OF THIS STUDYUse of randomised controlled design minimises selection bias and enhances internal validity.Stratified randomisation by World Federation of Neurosurgical Societies score ensures balance in clinical severity between groups.Single-centre design may limit generalisability to broader patient populations and healthcare settings.Blinded outcome assessment reduces risk of detection bias for follow-up measurements.Absence of interim analysis may delay detection of potential harm or benefit during trial progression.

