### Interventions

Patients in the intervention group will receive a high dose of LMWH, specifically nadroparin 5700 AxaIU administered two times per day. Treatment will start as soon as the redeemed safe is available, but no later than 24–72 hours after coiling and will continue for 21 days following the initial SAH. For safety reasons, high-dose nadroparin will only be administered to patients with a secured aneurysm. The current inclusion criteria consider both the time of ictus and the timing of coiling. Only patients who undergo coiling within 72 hours of ictus are eligible for inclusion, with most starting nadroparin within 24 hours after coiling. In clinical practice, the majority of eligible patients present on the day of ictus or the following day and are coiled within 24 hours. Since DCI typically develops between days 4 and 10 after SAH, this time frame is considered an appropriate therapeutic window. If discharged home before 21 days, the treatment will stop on discharge. If hospitalisation extends beyond 21 days, the prophylactic dose will be continued until discharge or until the patient is mobilised for more than 6 hours per day. The high dose of nadroparin used in this study is solely considered therapeutic in patients weighing under 70 kg. This fixed dosing approach reflects the study’s focus not solely on anticoagulant effects but also on the broader pleiotropic properties of LMWH, such as anti-inflammatory and endothelial-stabilising actions. In general, target anti-Xa levels for nadroparin are unknown. Based on observed anti-Xa levels in subjects with a therapeutic weight-based dose, reference ranges are regularly around 0.6–1.2 IU/mL. However, it remains uncertain whether benefits and harms of nadroparin are optimally maintained in this range.^28^

In the control group, patients will receive standard care with a prophylactic dose of LMWH (nadroparin; 2850 AxaIU once daily for those weighing ≤100 kg, or 5700 AxaIU once daily for those weighing >100 kg), starting within 24 hours after coiling and continuing until discharge or when mobilised for at least 6 hours daily.

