### Outcomes

The primary objective is to evaluate whether treatment with high-dose LMWH in patients with coiled aSAH significantly reduces mortality assessed at 30 days after the initial bleeding. Secondary objectives are to evaluate whether this treatment significantly reduces the presence and severity of DCI (measured by the Modified National Institutes of Health Stroke Scale),^29^ increases the incidence of major bleeding (defined as a fatal bleeding and/or symptomatic bleeding in critical areas or organs (such as intracranial, intraspinal, intraocular, retroperitoneal, intra-articular, pericardial or intramuscular bleeding causing compartment syndrome) and/or bleeding resulting in a haemoglobin drop of 1.2 mmol/L or more, or requiring a transfusion of two or more units of whole blood or red cells) and non-major bleeding (defined as all reported bleedings not classified as major),^30^ increases the risk of haemorrhagic complications after shunt placement or lumbar puncture, reduces other SAH-related complications (such as severe hyponatraemia, postprocedural aneurysm rupture, rebleeding, delirium, epilepsy, diffuse parenchymal swelling or nosocomial infections), reduces the incidence of shunt-dependent hydrocephalus, increases the rate of discharge to home, improves quality of life at 6 months, enhances cognitive functioning at 6 months, increases the likelihood of a favourable outcome at 6 months and reduces mortality at 6 months. Outcome assessments are done by a trial nurse at the outpatient clinic 6 months after the initial bleeding, with the standard follow-up performed on the same day. The trial nurse is blinded for group allocation and does not participate in the medical treatment of the included patients. In addition, peak anti-Xa levels are measured at 12:00 on day 7 following the ictus and are readily available for analysis. A comprehensive panel of coagulation and inflammatory biomarkers is also being collected and will be analysed after completion of patient inclusion. The biomarkers include von Willebrand factor, syndecan-1, soluble thrombomodulin, tumour necrosis factor-alpha, interleukin (IL)-6, IL-8, soluble vascular cell adhesion molecule-1, angiopoietin, a disintegrin and metalloproteinase with thrombospondin motifs 13, D-dimer and coagulation factor III (also known as tissue factor). All biomarker measurements are performed on day 7 following the ictus.

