### Sample size calculation

In our retrospective analysis, we found an 18% reduction in mortality when patients were treated with high-dose LMWH (23% mortality in the low-dose LMWH group versus 5% mortality in the high-dose LMWH group, OR 0.19, 95% CI: 0.07 to 0.55).^25^ Although this is a substantial reduction, it was derived from a retrospective, non-randomised design, which limits the ability to assess causal inference and make proper adjustments for confounding prognostic variables. Since we cannot assume this effect size to be accurate without further validation, we aim to conduct a phase II RCT with a total of 100 patients (50 patients per group). After the inclusion and follow-up of these patients, we hope to perform a more reliable power calculation to proceed to a phase III trial.^31^ Besides clinical data, this study will help evaluate the financial and logistical feasibility (including compliance to the study medication, data collection and costs) of establishing a full-scale study.

Each year, 120–125 patients with aSAH are admitted to the Amsterdam UMC, with 80–90 of these patients receiving coiling of the causative aneurysm. Considering the exclusion criteria, we estimate that roughly 25–50 patients per year could be eligible for the ISCHEMIA trial.

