### Data safety analysis

Adverse events (AEs) and serious AEs (SAEs) will be recorded in our electronic case report form (CRF). Only AEs occurring during hospital admission that are unrelated to the SAH must be reported to the institutional review board and principal investigator. All SAEs will be reported without undue delay after obtaining knowledge of the events. In this trial, certain SAEs are anticipated in patients with SAH, including severe hyponatraemia (serum sodium <125 mmol/L), hypokalaemia (serum potassium <3.5 mmol/L), fever, hydrocephalus, DCI, periprocedural aneurysm rupture, rebleed, delirium, Terson’s syndrome, epilepsy, diffuse parenchymal swelling, nosocomial meningitis, pneumonia and urinary tract infection. These expected SAEs will be recorded in the CRF and do not require further reporting.

A data and safety monitoring board (DSMB) is installed for this trial including a neurologist, neurosurgeon and independent statistician. The members are not involved in the trial and have no competing interests. Their tasks, responsibilities and working procedures are outlined in a charter. The DSMB will review safety data and the incidence of (S)AEs at three specified intervals: After 30, 60 and 100 patients have completed their 30-day follow-up. The DSMB will conduct ongoing safety surveillance, particularly regarding the occurrence of SAEs related to an increased risk of haemorrhagic complications. Additionally, the DSMB will advise on the continuation of the trial and may recommend the Steering Committee of the ISCHEMIA trial to terminate the trial if there is clear and substantial evidence of harm. No interim analysis is planned in this trial.

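### The third scheduled DSMB review falls at the full sample size, when its advice on continuing or stopping can no longer affect enrolment or high-dose treatment

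*Protocol article*

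**What the plan says.** The Data safety analysis section of the protocol article sets the DSMB's review points: "After 30, 60 and 100 patients have completed their 30-day follow-up". The same section says that the board advises on continuation and "may recommend the Steering Committee of the ISCHEMIA trial to terminate the trial if there is clear and substantial evidence of harm". It also provides for surveillance between meetings, with a focus on haemorrhagic events, and for prompt reporting of serious adverse events. Listed expected events, rebleeding among them, need only be recorded in the case report form. The board's working procedures are left to a charter that is not shown. No interim analysis is planned, and the strengths and limitations box concedes: "Absence of interim analysis may delay detection of potential harm or benefit during trial progression".

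The Sample size calculation section fixes the total at 100 patients, 50 per group. Under Interventions, high-dose treatment starts after coiling and "will continue for 21 days following the initial SAH"; after that, "If hospitalisation extends beyond 21 days, the prophylactic dose will be continued until discharge" or sufficient mobilisation. The primary objective under Outcomes is whether treatment "significantly reduces mortality assessed at 30 days after the initial bleeding". The abstract adds: "The trial includes a 6-month follow-up period".

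**The concern.** A scheduled safety review protects participants only if some are still to be randomised or are still receiving the treatment under review. The third review point equals the planned total and requires every patient to have reached day 30, which is after the last possible high-dose day. The power to recommend termination for harm then has no enrolment or high-dose treatment left to stop.

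The timing matters more here because the trial has no interim analysis, is open label, and tests a higher dose of a drug whose bleeding risk the Discussion acknowledges. Death is also common in this population, so an excess in one arm is hard to recognise from single event reports. It shows up more readily in cumulative tables prepared for a scheduled meeting. Of the three scheduled meetings, only the first two can change what happens to trial patients.

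**Working it through.** **Inputs from the protocol article**
- Review points: 30, 60 and 100 patients with 30-day follow-up (Data safety analysis).
- Total: 100 patients, randomised 1:1 (Sample size calculation; Allocation and randomisation).
- Last possible high-dose day: day 21 after the haemorrhage (Interventions).
- Day 30 of the mortality outcome is counted from the haemorrhage (Outcomes).
- Potentially eligible patients: 25 to 50 per year (Sample size calculation). Recruitment target: 100 within 4 years (Study design and setting).

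**The plan's own figure.** 100/25 = 4.0 years and 100/50 = 2.0 years, which agrees with recruitment within 4 years. The range of 25 to 50 per year is therefore a fair basis for the calendar.

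**Third review**
- Still to be randomised: 100 − 100 = 0.
- On high-dose treatment: 0, because day 21 comes before day 30 on the same clock. If the follow-up in the review schedule were counted from randomisation instead, the review would fall later still.

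**Second review.** When the 60th patient reaches day 30, others have been enrolled in the meantime. With uniform accrual at rate r per year and an immediate review, enrolled = 60 + r × 30/365.25.

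| | r = 25 | r = 50 |
|---|---|---|
| Enrolled during the 30-day lag | 2.05 | 4.11 |
| Enrolled at the second review | 62.05 | 64.11 |
| Still to be enrolled | 37.95 | 35.89 |
| Months to last enrolment (still to enrol / r × 12) | 18.2 | 8.6 |
| Months from review 1 to review 2 (30/r × 12) | 14.4 | 7.2 |
| Months from review 2 to review 3 (40/r × 12) | 19.2 | 9.6 |

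So about 36 to 38 patients are enrolled after the last scheduled review that can act, over about 9 to 18 months.

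**Sensitivity to the lag.** Randomisation follows the haemorrhage by some days. Coiling within 72 hours and a start within 72 hours of coiling allow up to 6 days, so the lag could be as short as 24 days. Then 40 − 25 × 24/365.25 = 38.4 and 40 − 50 × 24/365.25 = 36.7, so the picture is the same.

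**Scale of what falls in this period.** With 36 to 38 patients, each arm has 18 to 19. At the 23% in-hospital mortality of the low-dose group in the retrospective analysis (used only as an assumption for this trial), 18 × 0.23 = 4.1 to 19 × 0.23 = 4.4 control deaths would be expected.

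**An earlier third review**

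| Third review at | Enrolled (r = 25; 50) | Still to be enrolled (r = 25; 50) |
|---|---|---|
| 75 patients | 77.05; 79.11 | 22.9; 20.9 |
| 80 patients | 82.05; 84.11 | 17.9; 15.9 |
| 100 patients, as written | 100 | 0 |

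A third review at 75 to 80 leaves about 16 to 23 patients whose enrolment it can still affect.

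**The case against.** The strongest reply is that the reviews are not the DSMB's only safeguard. The same section provides for surveillance between meetings and prompt reporting of serious events, and it does not tie the power to recommend termination to the three meetings. Frequency and triggers of surveillance belong in a charter, and a condensed article need not give them. This stands, and it limits the point. It does not give the third meeting anything to act on, and the article alone cannot show that the surveillance replaces a scheduled look.

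Four stronger readings are tempting, and the documents do not support them.
- A reader might infer that patients 61 to 100 have no scheduled review. Their data are reviewed at 100. What they lack is a scheduled review while they are being enrolled and treated.
- A reader might infer that the board never sees rebleeds because they are exempt from reporting. The text says only that expected events are recorded in the case report form and go no further. It does not say that the board cannot see those data. Death is not on that list, and neither are most of the major bleeds defined under Outcomes.
- A reader might infer that nobody is on study drug at day 30. That holds for the high dose. Under Interventions, prophylactic nadroparin may continue in either arm until discharge or mobilisation, whereas the abstract gives up to 21 days for both arms. Those two statements need reconciling, but this point does not depend on them.
- A reader might infer that the reviews are the only look by arm. The article does not say whether they are by arm.

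It can also be said that a final review informs the remaining 6-month follow-up and the decision on a phase III trial. That is true, but a final safety report to the board would do the same. Lastly, every schedule leaves some patients after the last useful look, so the exact placement is a matter of judgement. Placing the last look at the full sample size is still hard to justify when an earlier one costs no more.

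**Conclusion.** The point holds in a limited form. By the article's own figures, only the reviews at 30 and 60 patients can affect enrolment or high-dose treatment. About 36 to 38 of the 100 patients are enrolled after the second, over about 9 to 18 months, with between-meeting surveillance and event reporting as their only stated DSMB protection during that time.

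The size rests on three assumptions: uniform accrual, enrolment equal to the stated number of potentially eligible patients, and a review held as soon as the count is reached. Slower enrolment would bring the number closer to 40 and lengthen the period. A delayed meeting would lower the number, by 25/12 = 2.1 to 50/12 = 4.2 patients per month of delay. None of these changes the result at the third review, where the number still to be enrolled is 0.

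No figure in the plan is wrong and patients 61 to 100 are not without oversight, so the severity is minor to moderate.

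**What to change.** If the third review has not yet been held, move it to before recruitment ends, for example when 75 to 80 patients have completed 30-day follow-up. Give the DSMB the data on all 100 patients afterwards as a final safety report. Randomisation began in January 2022 and the article does not say which reviews have taken place, so re-spacing all three may no longer be possible. Moving only the last one does not depend on that.

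If the date cannot be moved, state in the protocol or charter what the surveillance delivers for patients 61 to 100: how often the board receives cumulative tables, what triggers an unscheduled meeting, and how rebleeds recorded in the case report form reach it.

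The cost is a short edit to the protocol and the charter. The number of meetings is unchanged. No alpha is spent, because the reviews are for safety only, include no efficacy test, and lead to a recommendation to stop only for harm.

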## Ethics and dissemination

The protocol for this trial received approval from the Medical Research Ethics Committee (MREC) of Amsterdam UMC, location AMC in Amsterdam, the Netherlands (MREC-number 2020_192). The study will adhere to the principles outlined in the Helsinki Declaration. Results from this research will be submitted for publication in a peer-reviewed journal, and presented at national and international conferences.

### Patients and public involvement

Patients were not involved in the design, conduct, reporting or dissemination plans of this research.

## Discussion

The results of this phase II RCT will offer valuable insights into the efficacy and safety of high-dose nadroparin in patients with aSAH treated endovascularly. Our retrospective analysis suggests that high-dose LMWH may improve clinical outcomes by reducing in-hospital mortality and increasing discharge rates to home compared with standard prophylactic doses.^25^ The ISCHEMIA trial is particularly significant as it is the first to rigorously assess the impact of high-dose nadroparin in this patient population through a prospective, randomised design. Priorities of this trial are to further evaluate the clinical efficacy and safety profile of high-dose nadroparin, refine our power calculations and assess the financial and logistical feasibility of implementing this treatment regimen in the future. The additional data and revised methodologies will inform the design and implementation of a full-scale phase III trial. Given the case fatality rate associated with aSAH, we would consider an absolute mortality reduction of 5% or a relative risk reduction of at least 20% to be a clinically meaningful threshold to justify progression to a larger trial.

The anticipated benefits of high-dose nadroparin are based on its broad anti-inflammatory and immunomodulatory effects, extending beyond anticoagulation.^20 21^ By targeting key pathophysiological processes involved in DCI, such as cortical spreading depressions, endothelial dysfunction and neuroinflammation, nadroparin might mitigate secondary brain injury more effectively than current standard treatments. Given the complex and not fully understood mechanisms underlying DCI, this trial addresses an important gap in our therapeutic approach to aSAH. If proven effective, this treatment is expected to lead to improved clinical outcomes, reduced mortality and fewer SAH-related complications.

There are several strengths to this trial. Patients will receive high-dose nadroparin only during their hospital admission and for a maximum of 21 days, ensuring no postdischarge burden. Additionally, nadroparin is relatively inexpensive, suggesting that future implementation would face minimal financial constraints. The study includes both primary and secondary objectives, with secondary outcomes covering a wide range of clinical parameters, offering a comprehensive assessment of the potential benefits and risks of high-dose nadroparin. Rigorous methodology, including stratified randomisation and intention-to-treat analysis, enhances the reliability and validity of the results. By selecting 30-day mortality as the primary outcome, the study employs a clear, objective and clinically significant endpoint, reducing subjective interpretation and providing a definitive assessment of the treatment’s impact.

This trial has some limitations. As a phase II RCT with a small sample size, it lacks the power to provide definitive conclusions about the effect of high-dose nadroparin on mortality and other parameters, necessitating a larger phase III RCT for confirmation. The trial is not fully blinded. We opted for an open-label approach due to both practical and ethical considerations. Nadroparin carries a risk of bleeding, and early recognition of haemorrhagic complications is essential. Unblinding in response to clinical deterioration may delay critical decisions or lead to uncertainty in management. Moreover, the dosing regimens differ between groups: patients in the intervention group receive nadroparin two times per day, while those in the control group receive it once daily. This distinction makes full blinding unfeasible, as it would likely be apparent to both patients and care providers. Additionally, nadroparin has measurable pharmacodynamic effects—such as anti-Xa levels—which would further compromise blinding, as clinicians could infer treatment allocation from laboratory results. Using a placebo control with sham anti-Xa monitoring was considered but deemed both ethically and logistically challenging. Simulating treatment would require drawing blood and performing lab tests solely to maintain blinding, offering no clinical benefit and exposing critically ill patients to unnecessary procedures. To minimise bias, a blinded trial nurse was included, and the primary outcome—mortality—was selected for its objectivity and resistance to observer bias. A further limitation of the study is that not all patients may complete all dosages due to emergency interventions requiring temporary cessation of the study medication, such as lumbar punctures or ventricular catheter placements. The heterogeneity of aSAH patients and the exclusion of those with intraparenchymal haemorrhage or non-endovascular treatments complicate the generalisation of results to the broader aSAH population or to settings preferring different aneurysm occlusion methods, such as clipping. Preferably, a larger and more diverse population will be included in future trials to establish broader applicability, if deemed safe.

In conclusion, the pathophysiology of aSAH and particularly DCI is complex and not well understood. The outcomes of this trial will guide the feasibility and design of a larger phase III RCT, which is essential for establishing the definitive clinical utility of high-dose nadroparin in improving patients with aSAH outcomes. If the hypothesised benefits are confirmed, this study could lead to a paradigm shift in the management of aSAH, moving beyond the current focus on vasospasm prevention to a broader approach targeting multiple pathophysiological pathways. The findings may also have significant implications for healthcare costs and resource allocation, potentially improving both clinical and economic outcomes in this patient population.
